### Secondary effectiveness outcome measures

Difference in condition-specific quality-of-life (QoL) trajectory measured by the AUC for the single item ICIQ-Male SF QoL score recorded by participant questionnaire completed during clinical visits or by post or online at baseline, immediately prior to surgery, 1 week after catheter removal, at 3, 6, 9, 12 months after intervention, and at 18 and 24 months after randomisation, and additionally prior and subsequent to any surgical re-intervention.Difference in global sexual functioning trajectory measured by the AUC for the single-item International Index of Erectile Function (IIEF) male sexual QoL score recorded by participant questionnaire completed during clinical visits or by post or online at baseline, immediately prior to surgery, 1 week after catheter removal, at 3, 6, 9, and 12 months after surgery, and at 18 and 24 months after randomisation and prior and subsequent to any surgical re-intervention.Difference in generic QoL trajectory measured by the AUC for the EQ-5D five-level version (5 L) version total score based upon responses to five-dimension items and using UK population valuations (0 death to 1 full health) and visual analogue scale score (0 worse possible health state to 100 best possible health state). The EQ-5D will be included in participant questionnaires administered during routine clinical visit or by postal or web-based participant questionnaire at baseline, immediately prior to surgery, 1 week after catheter removal, at 3, 6, 9 and 12 months after intervention, 18 and 24 months after randomisation, and prior and subsequent to any surgical re-intervention.Difference in rate of improvement of urinary flow rate measured as part of routine care at baseline, 3 and 24 months with an increase in Q_max_ ≥10 ml/s from baseline taken to signify a successful outcome [21].Difference in rate of recurrence and need for further intervention recorded from the clinical record for those returning to the care of their original specialist with recurrent stricture, by patient questionnaire for participants seeking care elsewhere, and checked by the local trial research staff at 24 months after randomisation. Questionnaires regarding further intervention will be sent to participants at 24 months after their initial surgery (if this falls before the end of the study) and also at the end of the study (December 2017). For participants in whom the clinical record documents stricture recurrence but no further intervention has occurred, the relevant clinical information will be sent in anonymised form as a case vignette to an expert panel of five urology clinicians independent of the trial to determine whether or not there is a majority opinion that clinical recurrence of the stricture has been confirmed.

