### Trial interventions

Two surgical interventions will be investigated:Urethrotomy (standard)The standard intervention of endoscopic urethrotomy typically takes 45 minutes under general anaesthesia, with prophylactic antibiotic cover. With the patient’s legs partially elevated in supporting stirrups, the endoscope is passed along the lubricated penile urethra to locate the distal end of the stricture. A fine-calibre wire guide is then passed through the stricture to the bladder. Using this guide, the stricture is progressively divided longitudinally using the mounted scalpel in the dorsal ‘12 o’clock’ orientation until the proximal end of the stricture is reached. For short flimsy strictures, dilatation with the instrument may suffice without making a cut. The instrument is withdrawn and a 16 French calibre silicon catheter inserted through the urethra to the bladder and left on free drainage [15]. The patient recovers on the ward and is discharged according to local practice (NHS median stay is 1 day) usually with the catheter still in place. He returns to hospital after an interval or remains as an inpatient according to local practice (typically 2–3 days) for catheter removal and voiding check and then is followed up by outpatient review and urinary flow rate at 3, 12 and 24 months. According to the clinician’s policy at individual recruiting sites, and patient choice, participants may continue a programme of intermittent self-dilation (ISD) using a plastic catheter following urethrotomy.2.Urethroplasty (experimental)Open urethroplasty involves the reconstruction of the urethra through an appropriately sited longitudinal skin incision made in the perineum beneath the scrotum between the legs. It requires pre-operative X-ray urethrography. The surgery takes 2–3 hours under general anaesthesia with the patient’s legs partially elevated in supports and prophylactic antibiotic given. The bulbar urethra is located through the skin incision and mobilised. The strictured segment is incised longitudinally with the cut extending into visibly healthy urethra proximally and distally. For the majority of cases where the stricture is relatively long and dense, a graft of oral mucosa is inserted to widen the strictured area of urethra (patch urethroplasty) [16]. The graft (typically 5 cm by 2 cm) is harvested according to a standard technique from the inner cheek with the donor site left open to heal spontaneously or closed with sutures according to surgeon practice [17]. The graft is prepared, positioned appropriately, sutured to the cut urethral edges, and stabilised on the deeper tissues within the perineal wound. This incorporates the graft mucosal surface into the lumen of the urethra. For short supple strictures, simple excision of the scarred area and re-joining of the cut ends may be performed without a graft (anastomotic urethroplasty) [18]. A 16 French calibre silicon catheter is then passed to the bladder and left in situ on free drainage. The patient recovers on the ward before discharge home (NHS median stay is 2 days). The patient returns after an interval according to local practice (typically 2–3 weeks) for an X-ray urethrogram to check leak-free healing, and catheter removal. Follow-up comprises outpatient review and urinary flow rate at 3, 12 and 24 months. Some surgeons prefer a further urethrogram or endoscopic examination to be performed at about 12 months to ensure that no recurrence has occurred.Surgeons performing the procedures will be UK consultant, accredited urologists or senior urology trainees under consultant supervision. Endoscopic urethrotomy is a procedure that all operating urologists have competency for and will take place at the hospital site where the participant was randomised. Open urethroplasty is a specialised procedure carried out for trial participants by urologists recognised as being urethral surgeons by their employing NHS organisation. The surgery will be carried out at regional referral centres (which are all registered sites for the OPEN trial) to which participants will be referred using established routine NHS pathways for undertaking this surgery.

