### Trial procedures

Participants will complete patient-reported outcome measure (PROM) questionnaires at baseline and throughout their trial participation. The questionnaire consists of a six-item urinary symptom score, pictorial urine flow question, single-item condition-specific quality of life questions and the EuroQoL five-dimension questionnaire (EQ-5D). The baseline and pre-intervention PROMs will be completed in hospital. A PROM will also be provided to the participants at discharge from the hospital to complete 1 week after catheter removal. Further questionnaires will be mailed to participants at 3, 6, 9, and 12 months post intervention, at 18 and 24 months post randomisation, and at the end of the study (December 2017). The timing of follow-up points initially from intervention, and then later in the observation period from randomisation, ensures that participants complete an adequate number of questionnaires whilst allowing for the time between randomisation and undergoing the intervention. Participant costs questionnaires (PCQs) will be posted to patients at 6, and 12 months post intervention, and at 18 and 24 months post randomisation. Up to two reminders may be sent where participants fail to return the questionnaires. In addition, participants will be reviewed in clinic at 3 months post intervention and at 24 months post randomisation for adverse event review and a flow rate measurement. A further adverse event review will also take place at 12 months post intervention, either in clinic or during a telephone review. Case report forms (CRFs) for each visit will be completed by the research team. If a participant has a re-intervention whilst in the 24-month post randomisation follow-up period this data will be collected on an additional CRF, and patients will be asked to complete both a pre-intervention and 1-week post catheter removal PROM.

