### Study objectives

Primary objectives are:* To determine the relative impact on trajectory of symptom control as measured by the International Consultation on Incontinence Modular Questionnaire Male Short Form (ICIQ-Male SF) voiding symptom questionnaire over 24 months after randomisation.* To determine the incremental cost per quality-adjusted life year (QALY) at 24 months after randomisation.

Secondary objectives are:Clinical:* To determine the relative change in urinary flow rate at 24 months.* To determine the relative rate of recurrence and need for re-intervention up to 24 months.* To establish the safety profile of each procedure.* To determine the relative impact of symptom control and quality of life over the total study duration (summarised as median time since intervention).* To determine the relative rate of need for re-intervention over the total study duration (summarised as median time since intervention).Economic:* To estimate the incremental cost per QALY modelled over 10 years.

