### Statistical analysis

The primary outcome, AUC for the ICIQ-Male SF symptom score, will be generated for each participant using the trapezoidal rule. Symptom score data for participants who have missed a scheduled time point will be estimated using a multiple imputation approach to make use of partial outcome data [26]. Sensitivity analyses will be conducted to assess the robustness of the treatment effect estimate to these approaches. The primary outcome measure will be analysed using linear regression with adjustment for the minimisation variables [site of recruitment and time since last procedure (<12 months or ≥12 months)]. The main statistical analyses will be based on all participants as randomised, irrespective of subsequent compliance with the treatment allocation. Secondary outcomes will be analysed using generalised linear models with adjustment for minimisation and baseline variables as appropriate. All estimates will be presented with 95 % confidence intervals. Subgroup analyses will explore the possible modification of treatment effect by clinically important factors; time since last procedure (<12 months or ≥12 months) as a global measure of stricture severity, age, stricture location, and length. This will be done by including treatment-by-factor interactions in the model. All analyses will initially be performed on an intention-to-treat basis. We will consider additional analyses such as per-protocol depending on the levels of compliance with allocated treatment. Further analysis will explore the impact of variations in treatment delivered; such as use of anastomotic urethroplasty, use of intermittent self-dilatation after urethrotomy, and delay between decision to treat and undergoing the intervention. From the initial phase of recruitment we will report estimates of recruitment rates and potential participant availability, together with appropriate confidence intervals. There are no planned interim outcome analyses; all analyses will occur following completion of trial follow-up. Interim analyses will be performed if requested by the Data Monitoring and Ethics Committee (DMC). All analyses will be outlined in detail in a pre-specified statistical analysis plan.

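### The flow-rate objective is change at 24 months, but the outcome gives only a yes/no gain of at least 10 ml/s and does not say at which visit; a continuous, baseline-adjusted main analysis should be named

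*Protocol article*

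**What the plan says.** - **Objective** (Study objectives, first clinical secondary objective): "To determine the relative change in urinary flow rate at 24 months". This is a continuous quantity at one time point.
- **Outcome** (Secondary effectiveness outcome measures): "Difference in rate of improvement of urinary flow rate measured as part of routine care at baseline, 3 and 24 months". Success is then defined by a threshold on Qmax, namely a gain of "≥10 ml/s from baseline taken to signify a successful outcome". The success criterion is not attached to either follow-up reading.
- **Model** (Statistical analysis): "Secondary outcomes will be analysed using generalised linear models with adjustment for minimisation and baseline variables as appropriate".
- **Population** (Statistical analysis): "All analyses will initially be performed on an intention-to-treat basis". The same section defers detail to a pre-specified analysis plan, which is not shown.
- **Schedule.** Trial interventions says, for urethroplasty: "Follow-up comprises outpatient review and urinary flow rate at 3, 12 and 24 months", and gives the same times for urethrotomy. Trial procedures says: "participants will be reviewed in clinic at 3 months post intervention and at 24 months post randomisation for adverse event review and a flow rate". It allows the 12-month adverse event review to take place by telephone.
- **Re-intervention.** This is a separate secondary outcome. The Sample size calculation section assumes 50% versus 20% at 2 years. The patient-reported outcomes add assessments before and after any re-intervention; the flow outcome has no such addition.

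**The concern.** The objective and the outcome describe different quantities. One is an amount of change at 24 months. The other is a proportion of men passing a threshold, at a visit that is not specified. The phrase used for the outcome can be read as a mean change or as the proportion who improved, and generalised linear models fit both. Two analysts working from this text could report different flow results and each claim to follow the protocol.

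Two things are at stake. The first is precision: reducing a measured flow to pass or fail usually discards information. The second is interpretation. Flow is read at 24 months after randomisation and analysed as randomised, in a trial that expects many more re-operations in one arm than in the other. Good flow at that visit may therefore be the result of a second procedure, not of the allocated one.

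**Working it through.** **1. The plan's own figure.** No sample size is given for flow. The nearest stated figure is the primary outcome's 186 men with complete follow-up (Sample size calculation): difference 0.1, SD 0.21, 90% power, two-sided 5%.

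n per arm = 2 × (1.960 + 1.282)² × 0.21² / 0.1² = 92.7, so 93 per arm and 186 in total. This reproduces the stated number. It is used below only as a yardstick for how many men may contribute.

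**2. Information kept by a cut.** For normal data with equal SDs, the efficiency of comparing proportions relative to comparing means of the same variable is φ(z_p)² / [p(1 − p)]. Here p is the proportion passing the cut, z_p is the normal quantile at p, and φ is the normal density. At p = 0.5 this is 0.3989² / 0.25 = 0.637 (that is, 2/π).

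| Proportion passing | Efficiency | Loss | 186 men are worth |
|---|---|---|---|
| 50% | 0.637 | 36% | 118 |
| 30% or 70% | 0.576 | 42% | 107 |
| 20% or 80% | 0.490 | 51% | 91 |
| 10% or 90% | 0.342 | 66% | 64 |

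With standardised effects of 0.2 to 1.0 and a central cut, the loss is 36% to 38%, so the result does not depend on a very small effect.

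**3. The same loss as power.** Take a standardised effect of 0.1/0.21 = 0.476, borrowed from the primary outcome. It has 90% power with 93 per arm if flow is analysed as continuous. If 50% succeed in one arm, the other arm has Φ(0 + 0.476) = 68.3%. The pooled proportion is 0.5915, and the power of the two-proportion test is

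Φ{[0.183 × √93 − 1.96 × √(2 × 0.5915 × 0.4085)] / √(0.25 + 0.683 × 0.317)} = 0.72.

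Across success rates of 20% to 70% in the lower arm, power runs from 63% to 73%.

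**4. Dependence on distribution.** The document gives no flow SD, distribution or success rate. For a cut at the median, efficiency is 0.76 for a t distribution with 10 df and 0.96 with 5 df. It exceeds 1 with 4 or 3 df. The 36% is a floor for roughly normal data only.

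**5. Re-intervention.** Let s be the success rate in men not re-operated (assumed equal in both arms) and r the proportion of re-operated men who pass the cut at 24 months. With the protocol's 50% and 20%:

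- urethrotomy: 0.5s + 0.5r
- urethroplasty: 0.8s + 0.2r
- difference: 0.3 × (s − r)

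| r | s = 80% (assumed) | s = 50% (assumed) |
|---|---|---|
| 0% | 24 points | 15 points |
| 25% | 16.5 | 7.5 |
| 50% | 9 | 0 |
| 80% | 0 | −9 |

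The row r = 0% is what results if re-intervention counts as failure. Replacing s and r by mean flow in the two kinds of men gives the same expression, so a continuous analysis is diluted in the same way.

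**6. Schedule.** Trial interventions has flow at 12 months. Trial procedures and Secondary effectiveness outcome measures have it only at 3 and 24 months after treatment starts being followed or randomisation, as each section defines them. The statements differ and must be reconciled; this review does not say which is right.

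**The case against.** The strongest reply is that nothing here is settled wrongly. The objective keeps change in flow, the outcome never says the threshold is the only analysis, and the generalised linear models, adjusted for baseline variables, can take continuous Qmax. The threshold is referenced, and a clinically interpretable responder rate is a reasonable thing to report. The information loss is theory for normal data, and flow carries no stated power requirement. This part stands: a reader might infer that flow will be analysed only as yes/no, or that a third of the information is lost whatever the data, and the document supports neither.

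A reader might also infer that men re-operated shortly before month 24 are counted as successes. No section says so. The document is silent on flow after re-intervention, such a rule commonly belongs in the analysis plan, and a man would pass only if his 24-month flow exceeded baseline by the threshold and no other rule applied. Including flow after re-intervention is also a legitimate comparison in a pragmatic intention-to-treat trial. Nor would recurrences be hidden. Re-intervention and recurrence form their own secondary outcome, taken from records and questionnaires, with an independent panel for recurrence documented without further intervention. Finally, moving to a continuous analysis does not remove the dilution.

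On the schedule, one section describes clinical follow-up and the others trial measurements, and a 12-month reading does not enter a 24-month objective. That makes the difference minor.

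What the reply does not remove is the mismatch itself. The objective names a change at 24 months, and the only criterion given is a threshold with no visit attached.

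**Conclusion.** The concern holds as a mismatch between objective and outcome that is worth correcting, with medium confidence. If the responder result is the analysis, the loss is at least about 36% for roughly normal flow data, and 51% if 20% or 80% succeed. The size rests on an assumed distribution and success rate that the document does not give, and with heavy tails the loss may be smaller or absent. The re-intervention figures show that dilution could be material under the protocol's own 50% versus 20%. They also rest on assumed success rates, and they apply to the continuous and the binary analysis alike. The primary outcome, the sample size and the separate re-intervention outcome are unaffected.

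**What to change.** 1. State that the main flow-rate analysis is Qmax at 24 months after randomisation as a continuous outcome, adjusted for baseline Qmax and the minimisation factors (site and time since last procedure).
2. Keep the gain of at least 10 ml/s as a supportive responder analysis and tie it explicitly to the 24-month reading.
3. Add a supportive responder version in which re-intervention before 24 months counts as failure, reported beside the version that uses the observed flow. Say plainly that the continuous analysis includes flow after re-intervention, if that is the intention.
4. Reconcile Trial interventions, Trial procedures and Secondary effectiveness outcome measures on whether flow is measured at 12 months.

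The cost is wording in the protocol and analysis plan. Baseline and 24-month flow are already collected, and re-interventions within 24 months are already recorded on an additional case report form.

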## Discussion

There is continued uncertainty amongst clinicians and men suffering recurrent bulbar urethral stricture whether urethroplasty or urethrotomy represent the best treatment with no new trials identified in a recently updated Cochrane review [14]. This in turn makes it difficult for providers of healthcare to plan appropriate services. The OPEN trial therefore remains necessary to provide the required evidence of effectiveness and cost-effectiveness.

The timely recruitment of sufficient numbers of trial participants has been the key challenge to date (June 2015) for the OPEN trial. The incidence of recurrent bulbar urethral stricture is relatively low, so identifying potential participants has been difficult. Furthermore, eligible patients have the option of either treatment in standard care (urethrotomy or urethroplasty), and as a result they are more inclined to follow their individually preferred treatment pathway rather than accepting randomisation. This may be exacerbated by clinicians stating that one option is better than another. In the screening data collected to date, 66 % of potentially eligible patients declined entry to the trial due to having a preference for either treatment.

Data collection through return of PROMs has remained high throughout the trial (75–100 % return rate for differing time points). This is attributed to strategies designed to encourage men to return their PROMs; e-mail and/or text pre-notification of PROM delivery, mailed and telephone reminders of overdue PROMs, and monetary ‘thank you’ gifts (£25 gift voucher after randomisation, £25 gift voucher at 24 months after randomisation, and a further £25 gift voucher after completion of all follow-up data). The lowest return rate for the PROMs was at the 1-week post catheter removal time point (currently at 68 % return). These were initially sent by post to the patient after their surgery, which relied on the sites uploading the dates of surgery and catheter removal into the e-CRF immediately. Sites were then encouraged to give the patient these PROMs at discharge, which has caused an improvement in the return rates.

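### Recurrence can be detected more readily after urethroplasty because of an optional 12-month examination described for that arm only, and masking of the adjudicating panel to the operation is not stated

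*Protocol article*

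**What the plan says.** All references are to the protocol article.

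- **Source of recurrence data** (Secondary effectiveness outcome measures). Recurrence and need for further intervention are "recorded from the clinical record for those returning to the care of their original specialist with recurrent stricture", by questionnaire for men treated elsewhere, and checked by local research staff at 24 months after randomisation.
- **Adjudication** (same section). "For participants in whom the clinical record documents stricture recurrence but no further intervention has occurred", the case goes to a panel of five: the information "will be sent in anonymised form as a case vignette to an expert panel of five urology clinicians independent of the trial". The panel decides by majority whether clinical recurrence is confirmed.
- **Follow-up after urethrotomy** (Trial interventions). The man "then is followed up by outpatient review and urinary flow rate at 3, 12 and 24 months".
- **Follow-up after urethroplasty** (same section). "Follow-up comprises outpatient review and urinary flow rate at 3, 12 and 24 months". The next sentence adds: "Some surgeons prefer a further urethrogram or endoscopic examination to be performed at about 12 months to ensure that no recurrence has occurred". Nothing similar is described for urethrotomy.
- **Blinding** (opening of Methods/Design). Patients and surgeons cannot be blinded. Only the central staff who manage and prepare the data are named as blinded; the panel is not mentioned.

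**The concern.** Two features bear on the same outcome.

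First, the chance of a recurrence being found depends on how hard someone looks. If some urethroplasty men are imaged or scoped at about 12 months for that purpose and urethrotomy men are not, narrowing is more likely to be recorded in one arm than in the other at the same true rate.

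Second, the panel is the one step in assessing recurrence that could be shielded from the treatment received, in a trial where patients and surgeons cannot be. Removing a name does not remove a mention of a graft or of self-dilatation, either of which would point to the operation.

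Recurrence and re-intervention form a listed secondary objective, and trial data on the care of men whose strictures recur feed the 10-year economic model. A difference produced partly by detection would carry into both.

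**Working it through.** **1. Detection by arm.**

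| | Urethrotomy | Urethroplasty |
|---|---|---|
| Outpatient review and flow rate at 3, 12 and 24 months | yes | yes |
| Optional urethrogram or endoscopy at about 12 months to check for recurrence | not described | some surgeons |

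The Trial procedures section schedules trial clinic reviews with flow rate at 3 and 24 months and lets the 12-month adverse event review be done by telephone. Near 12 months, the contact required by the trial may therefore involve no examination.

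**2. Route from detection to outcome.** A narrowing found at the optional examination enters the clinical record. There are then two routes:

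- *No re-intervention.* This is exactly the kind of case sent to the panel. The panel can reject it, so it can filter over-detection. It cannot recover a recurrence after urethrotomy that nobody looked for and nobody recorded.
- *Re-intervention follows.* The case bypasses the panel and counts directly towards need for further intervention.

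**3. The plan's own figure for further intervention.** The Sample size calculation gives 48 men per arm for 50% v 20% at 90% power and 5% significance. The unpooled normal formula, two-sided, reproduces it:

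(1.960 + 1.282)² × (0.5×0.5 + 0.2×0.8) / 0.30² = 10.51 × 0.41 / 0.09 = 47.9, so 48 per arm.

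The pooled formula gives 52. The revised trial size of 186 men with complete follow-up is 93 per arm.

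**4. Sensitivity to extra detection (assumed values).** The article gives no rate of extra detection, so 2, 5 and 10 points are assumed.

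*(a) A true 50% v 20%, with extra events added to the urethroplasty arm.* For further intervention, these would be re-interventions prompted by the optional examination. Pooled formula:

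| Extra points | Observed difference | n per arm for 90% power | Power at 93 per arm |
|---|---|---|---|
| 0 | 30 | 52 | 99.3% |
| 2 | 28 | 60 | 98.3% |
| 5 | 25 | 77 | 94.7% |
| 10 | 20 | 124 | 80.0% |

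*(b) No true difference, 50% in both arms, 93 per arm.* The standard error is √(2×0.5×0.5/93) = 0.0733. With bias b, the two-sided type I error is 1 − Φ(1.96 − b/0.0733) + Φ(−1.96 − b/0.0733):

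| b | Type I error |
|---|---|
| 0.02 | 5.9% |
| 0.05 | 10.5% |
| 0.10 | 27.6% |

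If the planned difference is real, loss of power is minor except at the top of this range. The main problem is a biased estimate.

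**5. Masking of the panel.** No arithmetic applies. The safeguards stated are anonymity, independence from the trial and a majority vote. None of these is masking to the operation, and the article neither states such masking nor excludes it.

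**The case against.** The strongest reply is that the article is silent on masking, and silence is not an admission. How vignettes are built and redacted is detail that an article may leave to the full protocol, which is not shown. This stands. A reader might infer that the panel is unmasked, but the article supports only that masking is not stated.

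A reader might also take the Discussion remark "This may be exacerbated by clinicians stating that one option is better than another" as evidence that panel members are partial. It explains why eligible men decline randomisation and says nothing about adjudicators, so it cannot support panel bias.

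Nor does it follow that symptom-free narrowing can be found in one arm only. Both arms have flow-rate measurement, and endoscopy after urethrotomy is not excluded by being unmentioned. Men returning to their specialist with a recurrent stricture suggests presentation with a problem more than screening, and the panel may reject incidental findings. This reduces the likely effect but does not remove it: the additional look is described for one arm, and the panel sees only what was recorded.

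It is also tempting to express a panel effect as a share of the planned 30-point difference. That difference is for further intervention, and men reach the panel only if they have had none, so panel votes cannot change it. Only re-interventions prompted by the optional examination could.

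Finally, imaging or endoscopy may be the main evidence that a stricture has recurred. Withholding it could leave the panel unable to judge, and limiting the main outcome to recurrences triggered by symptoms or flow would redefine it. Both objections stand, so the fix does neither.

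**Conclusion.** The point holds in a limited form. Followed as written, the plan gives unequal opportunity to detect recurrence, and the panel cannot correct this for urethrotomy men who were never examined. Whether the panel is masked to the operation is left open.

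The net direction is uncertain. The size cannot be derived, because the article says neither how many surgeons use the optional examination nor how often it finds narrowing. The figures for 2, 5 and 10 points are assumptions that show sensitivity; they are not estimates.

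A reader might conclude that the recurrence result will be uninterpretable. The article does not support that: the bias may be small, the panel filters part of it, and its surveillance component works against the experimental arm. The primary outcome, the area under the curve of a patient-reported symptom score, is unaffected. This is an inexpensive improvement to a secondary outcome.

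**What to change.** In Secondary effectiveness outcome measures:

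1. State that vignettes have the allocated operation and procedure-identifying details, such as graft and self-dilatation, removed, while the findings needed to judge recurrence are kept. If the full protocol already provides for this, one sentence saying so is enough.
2. Record what triggered each recurrence: symptoms, flow rate, or the routine optional examination.
3. Add a sensitivity analysis of recurrence, and of re-intervention, that excludes events found solely by the optional 12-month examination, and report those events separately by arm.

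The main definition of the outcome and the care of the men stay as they are.

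The cost is an edited vignette template, one extra data item and one extra analysis, with no added staff or procedures. Some vignettes lose a little detail, and masking will be incomplete where the findings themselves reveal the operation. Recruitment began in February 2013, so for events already recorded the trigger would have to be read back from the clinical record.
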